### Participants

In South Africa, pregnant girls and women receive ANC and maternity services at outpatient clinics, community health centers, or midwife obstetric units (MOUs) within the primary health care system, which serves over 70% of the population. Pregnant adolescent girls and young women aged 13 to 20 years who had access to a mobile phone were eligible to be recruited to participate in the study. The Western Cape Department of Health provided information on priority communities and clinics where youth pregnancy rates were high and provided guidance on recruitment procedures. On the basis of these discussions, 16 community facilities that provided ANC (comprising public health clinics, community health centers, and MOUs) were identified for recruitment. The facilities were located in 4 of the 8 health subdistricts in Cape Town: Cape Town Eastern, Cape Town Northern, Mitchells Plain, and Tygerberg. Participants were recruited while attending ANC at these facilities. The research team discussed recruitment and data collection activities with the facility managers. Research assistants introduced the study to attendees in the antenatal service waiting areas. In some cases, facility staff referred the research assistants to potential participants. Participants were also recruited from communities via social networks. The research assistants explained the study to potential participants in their language of choice. The research assistants were fluent in English and either Afrikaans or isiXhosa, which are the 3 predominant languages spoken in Cape Town.

The study initially aimed to recruit participants who were up to 24 weeks pregnant to maximize their exposure to the messaging content over the duration of their pregnancies. However, a considerable number of pregnant adolescent girls and young women were beyond 24 weeks when approached during recruitment. Therefore, it was decided to recruit all pregnant adolescent girls and young women.

### Recruitment Procedure

A total of 20 trained research assistants conducted recruitment and data collection activities. Recruited participants received information sheets that described the objectives, benefits, and potential risks of the study; the dissemination of findings; the privacy and confidentiality of the study; and their right to withdraw from the study at any time. The participants were asked to complete a consent form (for participants aged ≥18 years) or assent form (for participants aged <18 years) before being enrolled in the study. In addition, parental consent forms were required for participants aged <18 years. Consenting individuals completed a self-administered baseline questionnaire on an electronic tablet or mobile phone. Baseline questionnaire completion was facilitated by the research assistants. In a few cases in which the participant was not comfortable with completing the questionnaire themselves, the research assistant administered the questionnaire. The questionnaire took approximately an hour to complete. Participants received a US $3 incentive for questionnaire completion.

User registration to receive the MomConnect and Teen MomConnect messages required information to be entered on the name, mobile phone number, age, language, and expected date of delivery (EDD) of users. These variables, as well as the estimated last menstrual date (LMD) and current enrollment in MomConnect, were extracted from the baseline data. In the few cases in which the participant did not have their own mobile phone, they were advised to enter into the baseline survey the mobile phone number of someone whom they lived with and whose mobile phone they could use to access the messages sent during the study. The EDD was required as messages are dependent on pregnancy week. In cases in which the EDD was missing, an estimate was calculated using the reported LMD. In cases in which both dates were missing, the participant was contacted telephonically several times to try to obtain either their EDD or LMD. The language was asked to assess the language in which participants would receive their messages. The options were English, Afrikaans, and isiXhosa. Participants were excluded from enrollment in the intervention study if one or more of their EDD, language, name, age, and mobile phone number was missing or if they were already registered on MomConnect.

Participants were then randomized to the experimental or control group using simple randomization (Figure 1). The study was blinded for participants as they were not told which group they were entered into. Participants were registered on the respective Teen MomConnect and MomConnect messaging programs in weekly or biweekly batches. The control group, which was registered in the MomConnect messaging program, received the MomConnect standard messages according to their pregnancy week and join week. The experimental group participants, who were registered in the Teen MomConnect messaging program, received the messages from the Teen MomConnect SMS text message library based on their pregnancy week, join week, and responses to the tailored questions. In addition, the experimental Teen MomConnect group were to receive 1 face-to-face behavioral counseling group session using MI administered by a trained research assistant.

**Figure 1 figure1:**
[figure not shown]
Diagram of the study procedure. AGYW: adolescent girls and young women; EDD: expected date of delivery; MI: motivational interviewing.

The research assistants contacted participants from September 2018 to December 2018 to schedule MI sessions at times that were convenient for them. Preliminary interview sessions revealed that some participants did not answer their phones, many scheduled sessions but did not attend them, many could not make time to attend a session because of school and other commitments, and it was difficult to allocate participants to times when all group members were available. Therefore, based on the ascertained limited availability of participants between enrollment into the study and the end of their pregnancy, it was decided to conduct motivational interviews with participants until 30% of the sample had received an interview session. Interview sessions could be conducted one-on-one or in groups of up to 5 people. Participants received an incentive of US $6 for attending a session.

Once the EDD had passed, participants in both the experimental and control groups were programmed to receive the standard postpartum messages that users receive in the MomConnect program. Participants were contacted a week after their EDD had passed to schedule voluntary completion of the follow-up questionnaire. Participants who had an abortion, miscarriage, or stillbirth were also contacted. As with the baseline questionnaire, participants completed the follow-up questionnaire on an electronic device facilitated by the research assistants, and they received a US $3 incentive. Electronic administration of both the baseline and follow-up surveys was facilitated using the Qualtrics electronic survey tool (Qualtrics International Inc) [43].

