**Methods:**

The intervention, Teen MomConnect, sent tailored motivational behavior change and behavioral reinforcement SMS text messages to participants about antenatal appointment keeping and pregnancy behaviors. The delivery methodology of the intervention was adapted from MomConnect, an mHealth education program for pregnant women in South Africa that has nationwide coverage. In addition, participants received a face-to-face motivational interviewing session delivered by a trained research assistant. Pregnant adolescent girls and young women aged 13 to 20 years were recruited from health facilities and community networks. Participants were randomized into the control group that received the standard MomConnect health SMS text messages or the experimental group that received the Teen MomConnect intervention. Participants completed a baseline questionnaire upon enrollment in the study and a follow-up questionnaire after the end of their pregnancy. The questionnaires assessed demographic characteristics, pregnancy behaviors, and the psychosocial determinants of antenatal appointment attendance (knowledge, attitudes, social support, risk perceptions, self-efficacy, intention, and action planning). Feasibility was assessed using descriptive analyses of acceptability, study implementation processes, and perceived satisfaction with the intervention. The number of appointments attended was obtained from the participants’ clinic records. Appointment attendance was compared between the control and experimental groups, as were awareness of HIV status and the psychosocial determinants of antenatal appointment attendance.

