### Objectives

There are currently few mHealth studies on interventions that are specifically targeted at improving health behaviors among pregnant adolescent girls and young women in LMICs [32]. Their behavioral, cognitive, and motivational needs and position in society are distinctly different from those of adult women. Therefore, this study sought to develop a mobile-based intervention targeting pregnant adolescent girls and young women. It adapts the MomConnect methodology. It includes motivational behavior change and behavioral reinforcement messages aimed at improving ANC attendance and its psychosocial determinants during pregnancy, as well as tailored message feedback on behavioral and psychosocial determinants. The intervention, titled Teen MomConnect, would be embedded in an SMS text messaging–based system similar to that of MomConnect. An additional component of the Teen MomConnect intervention is a motivational interviewing (MI) face-to-face counseling session delivered by research assistants. This paper describes the development and components of the intervention as well as the protocol for the pilot 2-arm randomized controlled trial (RCT) to evaluate the intervention’s preliminary efficacy and user acceptability.

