#### Development of the MI Content

The “Difficulty by Motivation” matrix for behaviors and interventions [36] guided the decision to supplement the messaging component with MI. Although tailored messaging can help change behaviors such as attending an appointment, complex behaviors where individuals show higher resistance to changing and require greater motivation and competence to change, such as sustained appointment adherence and substance abuse, often require more intense and interpersonal interventions such as MI. MI [37,38] is an evidence-based, patient-centered style of counseling that has been used in a range of health behavioral interventions in adolescents and adults. MI has been successful in improving health behaviors in pregnant women [39]. The aim of the MI session was to motivate and encourage the participants to attend ANC appointments and improve their health behaviors during pregnancy. MI differs from other types of counseling in that, instead of providing information and directive advice, the participants are encouraged to reflect on and express their own reasons for and against change and how their current behavior affects their life and family goals or core values and explore possible options for making change. Ambivalence and resistance are explored before moving toward action. The development of the MI content was informed by the key themes that emerged from the formative qualitative interviews previously conducted with pregnant adolescent girls and young women; focus group interviews conducted with health care workers and with research assistants who worked with the participants; and an analysis of the behaviors, social norms, and attitudes reported in the baseline questionnaire. The key themes of appointment keeping, substance use, HIV and tuberculosis testing, medication adherence, nutrition, and overall healthy pregnancy behaviors formed the basis of the MI content. The session was tailored to the participants to be relevant to their specific behaviors and questions. The MI sessions were first intended to be conducted by health care workers at the facilities. However, discussions with the facility staff revealed that they could not accommodate delivering these sessions into their already heavy workloads. Research assistants were then identified to conduct the sessions with the participants. The research assistants attended a training workshop facilitated by an expert counselor in MI. The training session taught reflective listening, asking open-ended questions, formulating affirmations, reflective listening, promoting change talk, and developing an action plan to improve behaviors identified as problematic. The research assistants were taught how to balance the expression of empathy with the need to build room for change. One face-to-face MI session was to be delivered by a research assistant during the participants’ pregnancies.

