## Discussion

### Synopsis

This paper describes the development of the Teen MomConnect intervention and the protocol for the pilot RCT to measure its feasibility and preliminary efficacy. The intervention aimed to improve antenatal appointment attendance among pregnant adolescent girls and young women using tailored 2-way messaging and MI. The results of the pilot study will inform policy makers and health program officers on how tailored, age-appropriate, and motivational health behavior messages can be delivered via mobile phone to large numbers of young people. The intervention expands the messaging content of the MomConnect program, which already has high coverage, to be relevant to youth. If the intervention shows promising results (eg, in terms of feasibility), it can be tested in a formal, fully powered trial. The findings will also show how the intervention was implemented and inform how it can be improved in the future.

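### Teen MomConnect is defined as tailored SMS plus one motivational interviewing session, but sessions stopped at 30% of an undefined sample, so the arm contrast is not the effect of SMS plus MI

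*Protocol article*

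**What the plan says.** All references are to the protocol article.

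- **Abstract, Methods**, as fact and without qualification: "In addition, participants received a face-to-face motivational interviewing session delivered by a trained research assistant".
- **Objectives**: "An additional component of the Teen MomConnect intervention is a motivational interviewing (MI) face-to-face counseling session delivered by research assistants".
- **Development of the MI Content**: "One face-to-face MI session was to be delivered by a research assistant", within the pregnancy.
- **Recruitment Procedure**, before Figure 1: "the experimental Teen MomConnect group were to receive 1 face-to-face behavioral counseling group session using MI".
- **Recruitment Procedure**, after Figure 1: because participants were hard to reach and to schedule, "it was decided to conduct motivational interviews with participants until 30% of the sample had received an interview session". The format changed too: "Interview sessions could be conducted one-on-one or in groups of up to 5 people".
- **Statistical Analysis**: MI attendance will be described, and exposure to MI is listed among the covariates of the regressions for attendance and its determinants.
- **Discussion, Synopsis**: the intervention aimed to improve attendance "using tailored 2-way messaging and MI". A fully powered trial may follow if results are promising, with feasibility given as an example.

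**The concern.** The label and the delivery differ. The label is SMS plus one MI session for the experimental group. The delivery rule is SMS for that group and MI for some of it, up to a fraction whose base is not stated. A reader of the abstract or the Synopsis alone would not learn that a cap existed.

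This affects how the efficacy result is read. A null result would say little about SMS plus MI if few women had MI. A positive result could be credited to a package that many, perhaps most, of the arm did not receive. The article itself argues, under Development of the MI Content, that harder behaviours such as sustained appointment adherence often need more than messaging. The partly delivered component is thus the one the authors saw as important for the attendance outcome.

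**Working it through.** **1. The plan's own power figure.** Inputs from Study Design: 100 per group, difference 0.52 visits, SD 1.3. Alpha is not stated; two-sided 0.05 is assumed.

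SE = 1.3 × √(2/100) = 0.184; 0.52/0.184 = 2.83; power = Φ(2.83 − 1.96) = 0.807. The noncentral t gives 0.804. The stated power of at least 0.80 reproduces.

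**2. MI coverage of the experimental arm.** Arm size 193 and total 412 are from Results; the planned 200 (100 per group) is from Study Design. Number with MI = 0.30 × base, rounded up; coverage = that number/193. This assumes that the cap was just reached and that all recipients were in the experimental arm.

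| Base of the 30% | With MI | Coverage of 193 | SMS only |
|---|---|---|---|
| Planned arm, 100 | 30 | 16% | 163 (84%) |
| Experimental arm, 193 | 58 | 30% | 135 (70%) |
| Planned sample, 200 | 60 | 31% | 133 (69%) |
| All enrolled, 412 | 124 | 64% | 69 (36%) |

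Two less likely bases give figures in between: 256 with follow-up gives 77 (40%), and 224 with records gives 68 (35%). The range is fourfold, and SMS only is the majority in every case but 412.

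**3. What partial coverage does to the arm difference (illustration).** Suppose the full package yields the planned 0.52 visits, MI carries a share s of that, and coverage is f. Then the arm difference is 0.52 × [(1 − s) + s × f]. The share s is not in the document, so a range is shown. MI is assumed to work equally in those who did and did not attend. Power is at 100 per group.

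| MI share s | f = 0.30: visits (power) | f = 0.64: visits (power) |
|---|---|---|
| 0 | 0.52 (0.81) | 0.52 (0.81) |
| 0.25 | 0.43 (0.65) | 0.47 (0.73) |
| 0.50 | 0.34 (0.45) | 0.43 (0.64) |
| 1 | 0.16 (0.13) | 0.33 (0.44) |

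Example: s = 0.50 and f = 0.30 gives 0.52 × (0.50 + 0.15) = 0.34.

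**4. What the planned covariate does.** Write the regression as attendance = a + b × arm + c × MI + other covariates. MI was assigned only to the experimental arm, so MI = 0 for every control. Leaving the other covariates aside, b is then the mean of experimental women without MI minus the control mean, which approximates SMS only versus control. The term c compares attenders with non-attenders inside one arm, after randomisation, and is open to selection.

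**5. Side by side.** Three different quantities are in play:

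- what the label implies: SMS plus MI versus control;
- what the as-randomised contrast gives without the MI term: SMS with MI for a subset versus control;
- what the arm coefficient approximates with the MI term: SMS only versus control.

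The article does not say which of these the efficacy conclusion will rest on.

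**The case against.** The strongest reply is that this is a disclosed change. The MI development section and the text before Figure 1 state an intention. The text after Figure 1 explains why it could not be met and gives the revised rule and format. MI attendance will be described, and MI enters the model, so partial delivery is acknowledged. In a feasibility pilot, low MI uptake is itself a finding. All of this stands, and nothing is concealed. It does not repair the abstract's sentence, supply the missing base, or say which effect the arm contrast estimates.

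Four stronger readings are tempting, and the document does not support them:

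- *Most women certainly had no MI.* If the base is all 412, up to 64% of the arm had it. The number who actually attended is not reported.
- *The Discussion already draws a wrong conclusion.* The Synopsis words state an aim. Efficacy results were still to be published, and progression is tied to promising results, with feasibility as the example. No result has yet been mislabelled.
- *Early enrolees could not receive MI because sessions ran only from September to December 2018.* Those months date the contacts made to schedule sessions. The article does not say that every session fell within them.
- *Restricting both arms to women due after 1 September 2018 would solve the problem.* Under assumed uniform enrolment and normally distributed gestation, this removes about 6% of the arm. Coverage with 58 recipients then moves only from 30% to 58/(0.94 × 193) = 32%, so the dilution remains.

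**Conclusion.** The point holds as a mismatch between the stated and the delivered intervention, together with an undefined cap. Coverage implied by the rule runs from 16% to 64% of the 193 experimental participants, and is 30% if the base is that arm. These figures assume that the cap was just reached and that only experimental participants had sessions.

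The as-randomised comparison remains valid for tailored SMS with MI delivered to a subset determined by availability. It is not an estimate of SMS plus MI. How far the two differ depends on how much of the effect MI carries, which the document does not say; if MI carries none, there is no loss. The planned MI covariate moves the arm coefficient further from the label. Delivery is finished, so this is a matter of definition and reporting. It should be settled before efficacy results are interpreted.

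**What to change.** 1. Correct the abstract so that it no longer says without qualification that participants received an MI session.
2. Reconcile Objectives, Development of the MI Content, the text before Figure 1 and the Synopsis with the text after Figure 1, using one description: tailored SMS for the experimental arm, with MI, one-on-one or in groups, conducted up to the cap.
3. State the base of the 30%. Report the cap and the number who received MI, each out of the 193 experimental participants.
4. Word the efficacy conclusion, and any go-ahead to a full trial, as the effect of the strategy as delivered.
5. State how this fits with exposure to MI as a covariate. If the conclusion concerns the strategy as delivered, it should come from the arm contrast without that term. If the term stays, say that the arm coefficient approximates SMS only versus control.

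The cost is wording, plus one count that the planned description of MI attendance should already supply. The conclusion becomes less favourable to the MI component.

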### Ethics Approval

The Research Ethics Committee of the Human Sciences Research Council (REC 2/17/08/16) granted ethics approval for this study. Permissions were obtained from the Western Cape Provincial Government and the Department of Health to conduct research within the communities’ public health clinics and MOUs.

### Measurement Instruments

Data were gathered from the baseline and follow-up questionnaires and from a review of patient clinical records at the facilities.

#### Questionnaires

Questionnaire development was informed by the reasoned action approach [44] and the Integrated Behavior Change Model (I-Change Model) [45], as well as a literature review on the psychosocial and socioeconomic factors associated with antenatal appointment attendance and health risk behaviors among young pregnant women.

The baseline questionnaire (Multimedia Appendix 2) assessed demographic characteristics; previous pregnancies; attitudes about the pregnancy; mental health status; knowledge of HIV and tuberculosis; HIV and tuberculosis testing; pregnancy risk behaviors (smoking, alcohol use, and illicit drug use); exposure to violence and harassment; perceptions regarding healthy pregnancy behaviors; knowledge regarding appointment attendance; risk perceptions; social support; peer norms; peer, partner, and family attitudes regarding appointment attendance; and participant attitudes, self-efficacy, action planning, and intention toward attending antenatal appointments.

The items on perceptions of healthy pregnancy behaviors, risk perceptions, social support, peer norms, attitudes, self-efficacy, action planning, and intention were all measured on a 4- or 5-point Likert scale, with responses ranging from *strongly disagree* to *strongly agree*.

Perceptions of healthy pregnancy behaviors included items on dietary behavior, nutrient intake, and physical activity. The perception statements were extracted from maternity health information booklets, including the Western Cape Department of Health “Caring for mothers, Caring for you” booklet. Exposure to violence was measured using 13 items on the lifetime frequency of exposure to violence or harassment from relatives, partners, teachers, or health care workers. The questions were adapted from the work by Reddy et al [26]. Knowledge of antenatal appointment attendance was measured using 16 statements informed by maternity booklets. Construction of the attitude, self-efficacy, peer norm, and intention items was based on the reasoned action approach by Fishbein and Ajzen [44], and the action planning, risk perception, and social support items were informed by the I-Change Model [45]. Risk perceptions referred to the perceived implications of not attending or missing antenatal appointments and the risks of pregnancy complications. Social support for attending ANC referred to the encouragement received from family, friends, and partners or boyfriends to attend appointments.

The follow-up questionnaire included the same items as the baseline questionnaire and additional items assessing the outcome of the pregnancy. In addition, evaluation questions were included in the follow-up questionnaire that assessed the participants’ experiences with the SMS text messages and the motivational interview content, overall satisfaction with the study, and experiences with the research assistants. Specifically, 21 items evaluated the messaging component by measuring comprehension, tone, appropriateness, and content of the messages; the perceived degree to which the messages motivated behavior change; the frequency of receiving the messages; and whether participants were able to respond to the messages. The items evaluating the MI were administered to those who reported attending a session. A total of 17 items assessed the perceived degree to which the MI session motivated behavior change, with responses on a 5-point Likert scale.

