### Primary and Secondary Outcomes

The primary outcome variables for feasibility were the perceived satisfaction and user acceptability of the intervention, whereas the outcome variable for assessing initial preliminary efficacy was the number of antenatal appointments attended. The number of antenatal appointments attended was obtained from the patient records at the facility. A secondary approach was to code the number of antenatal appointments attended into a binary variable for <4 versus ≥4 visits to calculate the proportion of participants who attended the requisite of at least 4 appointments during pregnancy [17]. Secondary outcomes were awareness of HIV status, psychosocial determinants of antenatal appointment attendance (knowledge, risk perceptions, attitudes, self-efficacy, intentions, and action planning), perceptions of healthy pregnancy behaviors, number of intervention messages responded to, and variables evaluating the recruitment and study implementation processes.

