### Statistical Analysis

Analyses will be conducted using SPSS (version 27.0; IBM Corp). Variables on perceived satisfaction with and acceptability of the Teen MomConnect messages and MI sessions in the evaluation section of the follow-up questionnaire as well as the number of messages responded to and MI attendance will be used for descriptive analyses to evaluate how the Teen MomConnect intervention was implemented and received. The outcomes of antenatal appointment attendance and its psychosocial determinants in the experimental (Teen MomConnect) and control (MomConnect) groups will be analyzed using linear regression for continuous outcomes and logistic regression for binary outcomes (including the outcome of percentage that attended ≥4 antenatal sessions) at follow-up. Covariates include age, race, previous pregnancies, school attendance, pregnancy week at enrollment, and exposure to MI. For outcomes related to knowledge, risk perceptions, attitudes, self-efficacy, intentions, and action planning scores that were measured at both baseline and follow-up, the change in mean values between baseline and follow-up in the experimental and control groups will be analyzed using analysis of covariance [46]. For each of these outcomes, moderation effects for race, gestational age at enrollment, socioeconomic status, age, and number of previous pregnancies will be tested with interaction terms in the regression models.

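### Motivational interviewing (MI) ratings come from women who say they attended a session, in either arm, with no stated check against the study's own attendance record

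*Protocol article*

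**What the plan says.** All references are to the protocol article.

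- **Role of the ratings.** Primary and Secondary Outcomes: "The primary outcome variables for feasibility were the perceived satisfaction and user acceptability of the intervention". Statistical Analysis puts the MI ratings under this outcome. Its descriptive evaluation uses "Variables on perceived satisfaction with and acceptability of the Teen MomConnect messages and MI sessions in the evaluation section of the follow-up questionnaire", together with MI attendance, for which no source is named.
- **Content.** Questionnaires: "A total of 17 items assessed the perceived degree to which the MI session motivated behavior change", answered on a 5-point scale.
- **Who rates.** Questionnaires: "The items evaluating the MI were administered to those who reported attending a session". The sentence does not mention the trial arm or a session record.
- **Delivery of MI.** In Recruitment Procedure, MI is planned for the experimental group only. After Figure 1 the text reports that "many scheduled sessions but did not attend them", and that interviews would continue until 30% of the sample had received one. It adds: "Participants received an incentive of US $6 for attending a session".
- **Timing.** "The research assistants contacted participants from September 2018 to December 2018 to schedule MI sessions". For follow-up: "Participants were contacted a week after their EDD had passed to schedule voluntary completion of the follow-up questionnaire".

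**The concern.** The filter asks who remembers, or believes, that she had a session. The outcome needs to know who had one. These groups can differ in two ways.

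- **Non-attenders included.** Some experimental-arm women booked a session and did not come, and participants were not told their group. Research assistants also met participants at baseline. A woman without a session could answer yes and then rate something other than MI.
- **Attenders missed.** A woman who attended but answers no is not shown the items, and her view is lost.

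The summary would then not describe the MI that was delivered. MI reached only a minority by design, so the rater group is small and a few misplaced women can matter. According to the Discussion, promising results, for example on feasibility, would lead to a fully powered trial, so the acceptability results carry weight.

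**Working it through.** The article states no figure for MI misreporting, so there is none to reproduce on this point. The check has three parts.

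**1. Is a better source than self-report likely to exist?** Stopping at 30% requires a count of women who had a session, and paying US $6 per attender requires knowing who came. Both imply an attendance record. Measurement Instruments, however, lists only the questionnaires and the clinical records as data sources. Nothing in the article links the MI ratings to a session or payment record.

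**2. How many raters could be false?** Inputs from Results: 193 women in the experimental arm, and follow-up of 256/412 = 62.1%. Input from Recruitment Procedure: 30%. Assumptions:
- The 30% refers to the experimental arm and was reached.
- Follow-up is equal across arms and between attenders and non-attenders.
- All attenders recall the session.
- Between 2% and 10% of non-attending responders report one wrongly. This rate is not in the article.

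Calculation:
- Attenders: 0.30 × 193 = 57.9. With follow-up: 57.9 × 0.621 = 36.0.
- Non-attenders with follow-up: (193 − 57.9) × 0.621 = 83.9.
- False raters at 2%: 0.02 × 83.9 = 1.7. Share: 1.7 / (36.0 + 1.7) = 4.5%.
- False raters at 5%: 0.05 × 83.9 = 4.2. Share: 4.2 / (36.0 + 4.2) = 10.4%.
- False raters at 10%: 0.10 × 83.9 = 8.4. Share: 8.4 / (36.0 + 8.4) = 18.9%.

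So about 2 to 8 of roughly 38 to 44 raters would be false. For the opposite error, each 10% of attenders who do not report their session removes 0.10 × 36.0 = 3.6, or about 4 genuine raters.

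The article does not define the denominator of the 30%. If it means all 412, attenders number 0.30 × 412 = 123.6, of whom 76.8 have follow-up. Non-attenders in the experimental arm with follow-up number (193 − 123.6) × 0.621 = 43.1. False raters at 2% to 10% are then 0.9 to 4.3, or 1.1% to 5.3% of raters. The problem is smaller on that reading.

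**3. How long is the recall period?** MI was to be given during pregnancy, with follow-up contact one week after the expected date of delivery. Taking 40 weeks to that date, a session in week g leaves 40 − g + 1 weeks:
- g = 36: 5 weeks, about 1.1 months.
- g = 20.8 (experimental-arm mean at enrollment): 20.2 weeks, about 4.6 months.
- g = 5: 36 weeks, about 8.3 months.

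The planned recall period is therefore about 1 to 8 months. Actual intervals are not reported.

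**The case against.** The strongest reply is that the sentence describes a skip question in an instrument already administered, not an analysis set. MI attendance is listed beside the number of messages responded to, which comes from the message server, so it may also come from study records. On this view the merge is detail for an analysis plan, and nothing in the article contradicts anything else. In addition, a separately arranged face-to-face session, paid at twice the questionnaire incentive (US $6 against US $3), is fairly easy to remember. The baseline was mostly self-administered on a tablet or phone, so confusing it with MI is only a possibility. The summaries are descriptive, in a pilot, with no test or threshold attached.

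Much of this stands. It lowers the likely misreport rate and the stakes, and the article does not show that attendance itself was taken from the questionnaire. It does not remove the point. The article states a rule for who supplies the ratings, and Statistical Analysis summarises those ratings without any restriction by arm or record.

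A reader might also join the first MI month (September 2018) to the last month of questionnaire collection (December 2019) and infer recall over about 15 months. The documents do not support that. It is the outer calendar span and ignores the planned contact one week after the expected date of delivery.

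**Conclusion.** The point holds in a limited form. A component of the primary feasibility outcome rests on self-reported attendance in either arm, with no stated check against a record the team very likely has. Non-attenders can be included and attenders missed. How often this happens is unknown. The 4% to 19% range for false raters depends on the assumed 2% to 10% misreport rate and on reading 30% as a share of the experimental arm. The sample size is not affected.

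Two stronger readings are not supported.

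- **A far larger false share.** Adding control women at the 10% rate gives 0.10 × 219 × 0.621 = 13.6 more false raters, and (8.4 + 13.6) / (36.0 + 8.4 + 13.6) = 38%. This stacks the highest assumed rate, the lower attender count and control-arm raters. The rule does not exclude control women, but nothing in the article says that any rated MI.
- **Ratings biased upward.** Unimpressed attenders may be the ones who forget, but false raters could score high or low. The net direction is not shown.

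**What to change.** In Statistical Analysis:

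- Limit the MI rating summary to experimental-arm women with a session in the session and payment records.
- Report agreement between self-report and record among follow-up responders, including a count of women who attended but did not report it. They were not given the items, so they can be counted but their ratings cannot be recovered.
- State that MI attendance is taken from the session and payment records.

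The analyses are described in the future tense, so this can still be specified. It needs one merge of the attendance records with the follow-up file and a few extra counts in the feasibility table. The drawback is slightly fewer raters.
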